### Data Analysis

For analysis, we will report contingency tables, whereby the primary outcomes will be treated as categorical variables. We will use Pearson's chi‐squared probability distribution to compare the three groups (two interventional and one control), whereby both independent (treatment: 3D virtual or 3D printed models) and dependent (PSMs) variables are categorical. Our null hypothesis is that there is no difference among these three groups. We will conduct analysis at the significance level of *P* = 0.05. We will report mean, variability and CIs for the control group and intervention arms of PSMs and functional outcomes. When analysing continuous variables resulting from questionnaires related to functional outcomes, we will conduct parametric (one‐way anova) and non‐parametric (Kruskal–Wallis test) tests depending on the tests of normality, and run an ancova, while adjusting for multiple comparisons (e.g. Bonferroni) and including pairwise comparisons (independent *t*‐tests).

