### Study Design

This is the design for a single‐centre parallel feasibility study consisting of two prospective intervention arms (a 3D printed model and a 3D virtual model), and a retrospective and a prospective control group (Fig. 1). Although this study will be non‐blinded for surgeons as they will be operating on patients using either of the models, it will be blinded for analysis. Note that this will not be a randomised study.

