**Fig. 1 bju16850-fig-0001:**
[figure not shown]
Flow of participants and execution of our feasibility study. RARP, robot‐assisted radical prostatectomy.

The aim of this study is to measure the effect of 3D models on the reduction of PSM rates and on functional outcomes after RARP. Our main hypothesis is that there will be a reduction of positive resection margins (PSMs) and improvement of functional outcomes for patients undergoing RARP when surgeons are presented with a 3D printed or 3D virtual patient‐specific prostate model during surgery. Specifically, we hypothesise that 3D models reinforce the mental reconstruction of the anatomy that surgeons acquire via conventional 2D mpMRI whilst assisting surgeons in matching the precise location of the anatomy and lesions with respect to the endoscopic view they observe during RARP [10]. 3D models could inform the surgical management and nerve‐sparing technique, whilst avoiding increases in PSM rates. Studying both 3D virtual and 3D printed models will allow us to understand whether tactile information is important. We highlight the importance of recruiting surgeons across different levels of expertise to reduce bias and avoid having expertise as a confounder for the impact of 3D models on the reduction of PSMs. Therefore, we will stratify our results based on each surgeon's number of years of experience.

We will also report measures related to the deployment of this feasibility study in anticipation of a subsequent larger randomised controlled trial. Measures include patient recruitment rate, and percentage of cases that led to successful model deployment in the operating theatre.

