### Endpoints

The primary study outcome is PSM rates measured after specimen analysis. Secondary outcomes include incontinence rates (pad weights, electronic Patient‐Reported Outcome Measures), erectile dysfunction (International Index of Erectile Function score, and Erectile Hardness Score), and International Consultation on Incontinence Questionnaire‐Urinary Incontinence (ICIQ‐UI) score captured at 3 months after surgery. Other secondary outcomes are related to our pipeline deployment metrics, including patient recruitment rate and percentage of cases that led to successful model deployment in the theatre.

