#### Surface Model Generation

Labels resulting from segmentation will be processed through a pipeline specifically developed for our study. This pipeline will create labels either for 3D virtual models or for 3D printing.

Patients will be assigned to one of the intervention groups based on the resources available to produce 3D printed or 3D virtual models in a timely manner before surgery (Fig. 2). Specifically, the allocation to an intervention arm will be carried out based on the time that the anonymised data are received by the engineering team and the remaining days before surgery to allow the generation of 3D models. Note that virtual models are faster to generate compared to printed models.

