#### Control Group

Patients will be prospectively assigned to a control arm according to our inclusion/exclusion criteria. We aim to include cases following 1:2 propensity‐score matching with respect to intervention arms. These cases will be pseudo‐anonymised and data collected will include patient demographics, mpMRI, PSM status, and functional outcomes. For comprehensiveness, we also aim to include retrospective cases observed over the same period of time as the execution of our feasibility study, according to our inclusion/exclusion criteria. This prospective vs retrospective analysis will allow us to measure for any possible bias and validate whether the intervention arms have impact in comparison with historical data. A search for retrospective cases will be conducted over the same period of time as the execution of our feasibility study to reflect similar practice. However, given that bias might be introduced due to the nature of a retrospective arm, we will additionally include cases as part of a prospective control arm during the execution of our study, but only if there are enough cases after interventional arm assignments.

#### 
Three‐dimensional Printed Intervention Arm

Patients will be prospectively recruited to obtain 3D printed models to surgeons at the start of RARP. These models will be printed by Guy's and St Thomas' Hospitals 3D printing facilities, using an Object500 Connex1 polyjet 3D printer (Stratasys, USA). As part of the design of this protocol, we have developed a bespoke additive manufacturing workflow to meet the requirements of our patient‐specific 3D printing task. The aims of our workflow are: (i) to maximise the clarity with which tumour lesions can be discriminated from healthy glandular tissues, and (ii) to minimise geometrical deviation from the virtual model obtained from segmentation on mpMRI. Our workflow meets these ambitions by leveraging multiple materials (with visually contrasting properties) and multi‐part assembly (to eliminate the need for abrasive post‐processing). The geometrical accuracy of the following patient‐specific 3D printing specification was validated using a coordinate measuring machine (Faro, USA): disagreement between 3D printed and virtual surfaces (see Fig. 3, right panel).

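### The primary PSM test is a crude three-group chi-squared in a non-randomised study, so residual differences in stage, grade or surgeon may be read as effects of the 3D models

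*Protocol article*

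**What the plan says.** - **Design.** Study Design states: "Note that this will not be a randomised study".
- **Primary outcome.** Endpoints: "The primary study outcome is PSM rates measured after specimen analysis". For each patient this is a yes/no result.
- **Primary test.** Data Analysis uses Pearson's chi-squared "to compare the three groups (two interventional and one control"), on a contingency table of treatment by PSM at the 0.05 level. No covariate, stratum or matched set is mentioned.
- **Adjusted analysis.** ANCOVA is named only in the sentence that opens "When analysing continuous variables resulting from questionnaires related to functional outcomes". It does not reach PSM.
- **Printed or virtual.** Surface Model Generation says that "the allocation to an intervention arm will be carried out based on the time that the anonymised data are received by the engineering team", together with the days left before surgery.
- **Controls.** The Control Group section says: "We aim to include cases following 1:2 propensity‐score matching with respect to intervention arms". The variables in the score are not named. The prospective controls are to be included, "but only if there are enough cases after interventional arm assignments".
- **Surgeon.** Study Design (text after Fig. 1) plans to recruit surgeons of differing expertise to "avoid having expertise as a confounder for the impact of 3D models on the reduction of PSMs", and to stratify results by years of experience. How that stratification enters the PSM analysis is not said.
- **Restriction.** Eligibility Criteria limit entry to T2–T3a lesions at the capsule and near the neurovascular bundles, with Gleason 3 + 4 or higher.

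**The concern.** A crude chi-squared test keeps its 5% error rate, as a test of the models, only if the three groups would have had the same PSM risk without them. Randomisation would give that on average. Here it depends on matching that is an aim, on the supply of left-over cases, and on the accidents of scheduling.

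The article itself gives reasons to doubt equal risk. Its Background says that many covariates affect outcome, naming surgeon expertise and lesion location. Eligibility still spans T2 to T3a and all grades from 3 + 4 upward.

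The stated aim is causal: to measure the effect of the models on PSM rates. The Discussion also intends the printed-versus-virtual comparison to guide the choice of model for a later randomised trial. That comparison has the least protection, because matching controls to each arm does not make the two arms alike, and time before surgery may track urgency or the surgeon's list.

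**Working it through.** **1. What the stated safeguards cover**

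| Safeguard | Control vs models | Printed vs virtual | In the stated PSM test? |
|---|---|---|---|
| Eligibility limits | partly | partly | by restriction only |
| 1:2 propensity matching | yes, if achieved | no | no |
| Stratification by surgeon experience | for surgeon only | for surgeon only | not stated |
| ANCOVA | functional scores only | functional scores only | no |

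**2. Matching arithmetic.** Two controls for each of 54 + 54 = 108 intervention patients would need 216. The plan has 108 prospective controls, or 108 + 54 = 162 with the retrospective ones. So 1:2 holds only arm by arm (2 × 54 = 108), with the same controls serving both arms.

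**3. How an imbalance reaches the result**

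Inputs from the article: control PSM about 20% (Sample Size Determination) and group sizes 54, 54 and 108. The test names one control group; I take it to be the 108 prospective controls.

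Assumed, because the article gives no figures: stage-specific PSM rates of 10% (T2) and 35% (T3a), or more mildly 15% and 30%; the size and direction of the stage imbalance; and no effect of the models.

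With T3a share s, the group's PSM rate is

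p = r(T2) × (1 − s) + r(T3a) × s.

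Setting p = 0.20 in controls gives s = (0.20 − 0.10)/(0.35 − 0.10) = 0.40, or (0.20 − 0.15)/(0.30 − 0.15) = 0.33. An imbalance d in the T3a share moves the crude contrast by d × (r(T3a) − r(T2)). For d = 0.20 that is 0.20 × 0.25 = 5 points, or 0.20 × 0.15 = 3 points.

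**4. Rejection rate of the 2-df Pearson test at 5%, by simulation, no true effect**

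| T3a share in the model arms, relative to control | Spurious PSM difference (15/30% to 10/35%) | Rejection at 15/30% | Rejection at 10/35% |
|---|---|---|---|
| equal | 0 | 5% | 5% |
| both 10 points lower | 1.5 to 2.5 points | 5% | 6% |
| both 20 points lower | 3.0 to 5.0 points | 7% | 11% |
| both 30 points lower | 4.5 to 7.5 points | 10% | 23% |
| one 20 lower, one 20 higher | 3.0 to 5.0 points each way | 10% | 19% |

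In the last row the two model arms differ from each other by 6 points (17% vs 23%) or 10 points (15% vs 25%) with no model effect at all. A stage-stratified Cochran–Mantel–Haenszel test on the same simulated data stays at about 5% in every row.

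**5. Events available for adjustment.** If PSM is 10% in the model arms: 108 × 0.20 + 108 × 0.10 = 32.4, about 32. If there is no effect at 20%: 216 × 0.20 = 43.2, about 43.

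**The case against.** The article does plan to control confounding, through matched controls, narrow eligibility and stratification by surgeon experience. If matching succeeds on stage and grade, a chi-squared test on the matched groups is not confounded by them, and ignoring the matched sets is then mainly a matter of variance. The score variables and sensitivity models are also details that a condensed article commonly leaves to the full protocol or SAP. And this is a feasibility study ahead of a randomised trial.

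Much of this stands. A reader might infer that case-mix differences will be reported as model effects, or that nothing in the design guards against them. The documents do not support that: the safeguards exist, and with a residual 10-point stage imbalance in both model arms the false-positive rate is still only 5–6%. A reader might also take the 23% figure as the expected harm. It needs a 30-point imbalance, which is close to matching having failed, and no document figure gives its size or direction. Nor does the article say that expertise is a confounder in this study; it says that recruitment is meant to prevent that.

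Two things survive. The test is not left open: its variables and null hypothesis are stated, and they leave out the matching and the stratification. And no matching or adjustment is described between the printed and virtual arms.

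**Conclusion.** The concern holds as a risk of residual confounding in the primary result, not as a certain bias. For controls against models, the risk depends on how well matching works, and effective matching on stage would remove the part due to stage. For printed against virtual, the stated protection is only eligibility and the stratification by surgeon experience, and an opposite 20-point stage shift would raise rejection to about 10–19%. All the rejection rates rest on assumed stage-specific PSM rates and assumed imbalances, with control PSM held at 20%; they are conditional illustrations. The point should be fixed, but the feasibility purpose keeps it below a must-fix.

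**What to change.** - Make the primary PSM estimate an adjusted one: three-group propensity weighting, or a parsimonious logistic model that respects the matching. Report risk differences with robust 95% confidence intervals.
- Name the covariates before outcomes are seen, and use those available in every group: preoperative T stage, Gleason group, and surgeon or surgeon experience. Add lesion size or side only if it can be read for controls without new segmentation. The Control Group section lists mpMRI among the control data, but nowhere does the article say that controls are segmented.
- Take the printed-versus-virtual contrast from the same model.
- Keep the crude chi-squared table as descriptive.

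The cost is a change of analysis text and some analysis work; no change to conduct is needed if the covariates are kept to those above. The downside is some model dependence with only about 32 to 43 events, which is why the outcome model should be small or the covariates placed in the propensity model.

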**Fig. 3 bju16850-fig-0003:**
[figure not shown]
Left: segmentation of patient‐specific prostate anatomy on multiparametric MRI (mpMRI) to extract annotations of the prostate gland (shown in translucent white), tumour lesions (shown in red), external sphincter (shown in purple), urethra (shown in yellow), and neurovascular bundles (shown in blue and green). Right: annotations resulting from segmentations are three‐dimensional (3D) printed and scanned using a coordinate measuring machine that captures a 3D representation of the physical model. The overlapping of annotations (in pink) and scanned 3D representation (in blue) validates that 3D printed models and 3D virtual models fully correspond to each other.

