### Sample Size Determination

This study will be conducted in a total of 270 patients: a prospective control group (*N* = 108), a retrospective control group (*N* = 54), a prospective 3D printed intervention arm (*N* = 54), and a prospective 3D virtual intervention arm (*N* = 54).

The sample size (*N* = 270) was computed based on a two‐arm study at 0.05 significance level in combination with Dunnett's correction, 0.75 power size, 0.25 interesting treatment effect, and equal standard deviations of 0.5 across arms for a normally distributed primary outcome using a ‘multiarm’ web tool (https://mjgrayling.shinyapps.io/multiarm) [18]. Based on our eligibility criteria controlling for patients with pT2 and pT3 lesions, we hypothesise that we will observe a PSM rate of approximately 20% in our control group, as evidenced from previous studies [15, 19].

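### The only PSM test is an undirected three-group chi-squared test, so no model-versus-control difference is planned, although the hypothesis and the Dunnett sizing both call for one

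*Protocol article*

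**What the plan says.** Study Design states the main hypothesis as fewer PSMs and better function "for patients undergoing RARP when surgeons are presented with a 3D printed or 3D virtual" patient-specific model. It adds that studying both kinds will show whether tactile information matters. The Discussion says the comparison of the two will help choose the model type for a later randomised trial.

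Sample Size Determination works at a "0.05 significance level in combination with Dunnett's correction", with "0.75 power size", an effect of 0.25 and a standard deviation of 0.5. The groups are 54 printed, 54 virtual, 108 prospective controls and 54 retrospective controls. A control PSM rate of about 20% is expected.

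Data Analysis plans a Pearson chi-squared test "to compare the three groups (two interventional and one control"). The null is stated: "Our null hypothesis is that there is no difference among these three groups". The level is 0.05. Means, variability and confidence intervals are promised for the control group and the intervention arms. Pairwise comparisons and a multiplicity adjustment appear only for the continuous questionnaire outcomes. The section does not say which control group is the one used.

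**The concern.** Three parts of the article describe the primary question differently. The hypothesis is directional and sets having a model against having none. The sizing compares each model with control. The test asks only whether any of three proportions differ.

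A significant omnibus result would therefore not establish the hypothesis: it does not say which group differs or in which direction, and a printed-versus-virtual difference alone can produce it. Nor does the plan call for a PSM difference from control with an interval, which is the quantity needed to plan the later randomised trial.

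**Working it through.** Rates below are in the order printed / virtual / control. Group sizes are 54 / 54 / 108, taking the prospective group as control. Tests are two-sided at 0.05 and ignore matching. Simulated figures use 400,000 trials per scenario.

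**1. The plan's own sizing.** With allocation 1:1:2 the two comparisons with control have correlation (1/108)/(1/54 + 1/108) = 1/3. The one-sided 0.05 Dunnett critical value is then 1.936. The expected statistic for each comparison is 0.25 / (0.5 × √(1/54 + 1/108)) = 3.0. The probability that both comparisons exceed 1.936 is 75.4%, and 54 + 54 + 108 = 216 is the smallest 1:1:2 design reaching 75%. Adding 54 retrospective controls gives 270. The article states neither sidedness nor the type of power; this variant reproduces its group sizes. The design calculation is thus consistent with each model being compared with control.

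**2. What the planned test reacts to.** Its power depends on λ = Σ nᵢ(pᵢ − p̄)² / [p̄(1 − p̄)], whatever the source of the spread. At 10/30/20%, p̄ = (5.4 + 16.2 + 21.6)/216 = 0.20 and λ = (54 × 0.01 + 54 × 0.01 + 0)/0.16 = 6.75. On 2 df this gives about 64% power; simulation gives 65%. The average model rate equals the control rate, and an any-model-versus-control test rejects in 4.7%. These rates are an illustration, not a prediction.

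**3. Three-group test against pooled 108 versus 108.** The 20% control rate is the article's; the 33%, 25%, 35% and printed 10% come from earlier studies cited in its Discussion. Other rates are assumptions.

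| PSM rates | Three-group test | Pooled test |
|---|---|---|
| 10/10/20% | 42% | 55% |
| 17.5/17.5/35% | 75% | 84% |
| 25/25/33% | 19% | 26% |
| 6/14/20% | 57% | 55% |
| 10/20/20% | 30% | 16% |
| 5/15/20% | 66% | 55% |
| 10/25/35% | 91.5% | 84.6% |

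Pooling gains when the models work about equally. With the average model rate held at 10%, the gain is gone once the arms differ by about 8 points.

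**4. Precision at 20% versus 10%.** The 95% half-width for any model versus control is 1.96 × √(0.16/108 + 0.09/108) = 9.4 points. For one model versus control it is 1.96 × √(0.16/108 + 0.09/54) = 11.0 points, or 12.5 points with the two-sided Dunnett value 2.227 in place of 1.96.

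**5. Testing single models only after a positive pooled test.** At 5/20/20%, the effective model is declared in 69% of trials by Dunnett directly and in about 31% behind such a gate. At 10/20/20% the figures are 26% and 12%.

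**6. Which control.** At 20% versus 10%, pooled power is 54% by formula against the 108 prospective controls, 43% against the 54 retrospective controls and 60% against all 162. The phrase in Data Analysis leaves this open.

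**The case against.** The strongest reply is that the arms are kept apart on purpose. The article wants to know whether touch matters and which model to take forward, and Dunnett's correction fits that aim. The hypothesis, "when surgeons are presented with a 3D printed or 3D virtual patient"-specific model, can be read as each model against none. This stands, and it rules out replacing the three-group structure with a pooled primary test or gating the single-model comparisons behind one. It does not rescue the chosen test: each model against none is not tested for PSM either.

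Second, a reader might justify pooling from the Fig. 3 caption, which "validates that 3D printed models and 3D virtual models fully correspond to each other". The caption concerns geometric agreement, not equal clinical effect. The only model-specific PSM rates in the Discussion are unequal: 10% printed, from ten patients, and 25% virtual. They come from separate cohorts and are only illustrative, but they give no support for assuming a common effect.

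Third, the contingency tables would let anyone compute a difference, and an unseen analysis plan may contain one. Both are fair, so the effect is not lost beyond recovery. But the article itself fixes the test, the null and the level, and what it fixes matches neither the hypothesis nor the sizing.

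**Conclusion.** The mismatch is real and cheap to correct. The PSM analysis as stated can reject without any average benefit of models (65% at 10/30/20%) and plans no effect against control.

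Two stronger readings are tempting. One is that any model versus control is the best-powered contrast and should come first. That holds only if the two models work about equally: 55% against 42% at 10/10/20%, but 16% against 30% at 10/20/20%. The other is that pooling escapes the allocation problem. It removes only the split between printed and virtual, which Surface Model Generation bases on resources and days before surgery. The choice between model and control is also non-random: Control Group adds prospective controls only if enough cases remain after the intervention arms are assigned. A narrower interval does not remove that bias.

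The power figures assume 54/54/108 independent patients, the prospective group as control and the rates shown. Matching or a shortfall of controls would change them.

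**What to change.** In Data Analysis:

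- Name the prospective group as the control for the PSM comparison.
- Add PSM risk differences with 95% confidence intervals for (a) any 3D model (108) versus prospective control (108) and (b) each model versus prospective control, with Dunnett adjustment for (b) to match the sizing.
- Estimate all of them in the propensity-matched set described under Control Group. Say how the 1:2 ratio applies: 54 to 108 is 1:2 for one arm, but 108 to 108 is 1:1 for both arms together.
- Report all of them whatever the omnibus result, with no gating of (b) behind (a).

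The cost is a few sentences, a little more analysis and one more reported contrast. No new data are needed. The Dunnett-adjusted intervals are somewhat wider (12.5 against 11.0 points in the example above). If the full analysis plan already contains these contrasts, one sentence in the article saying so is enough.

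### The sample size is set for comparing each 3D model with control, but the only planned PSM test is a non-directional three-group chi-squared, so the stated 0.75 power belongs to a different test and a significant result would not show which model, if either, lowers PSM.

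*Protocol article*

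**What the plan says.** Three parts of the protocol article bear on this.

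- **Study Design** (text after Fig. 1) gives a directional hypothesis: "there will be a reduction of positive resection margins (PSMs) and improvement of functional outcomes for patients undergoing RARP" when the surgeon has a printed or virtual model.
- **Sample Size Determination** uses "0.05 significance level in combination with Dunnett's correction", with "0.75 power size", "0.25 interesting treatment effect" and "equal standard deviations of 0.5 across arms for a normally distributed primary outcome". It does not say whether the test is one- or two-sided. It also does not say whether the power is for each comparison, for both, or for at least one. The groups are 54 printed, 54 virtual, 108 prospective control and 54 retrospective control.
- **Data Analysis** plans a Pearson chi-squared comparison of two intervention groups and one control group on PSM at 0.05, and states: "Our null hypothesis is that there is no difference among these three groups". Pairwise comparisons and adjustment for multiple comparisons appear only in the sentence on continuous functional outcomes. For PSM, the section otherwise promises contingency tables, group summaries and confidence intervals.

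**The concern.** Dunnett's procedure answers two questions: is printed better than control, and is virtual better than control? The chi-squared test on 2 degrees of freedom answers one question: do the three PSM rates differ in any way? It can reject because one model is better than control, because one is worse, or because the two models differ from each other.

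Two things follow. The power quoted in Sample Size Determination does not describe the test in Data Analysis. And the only formal PSM test cannot support the hypothesis in Study Design, nor say which model to take into the later randomised trial, which the Discussion gives as a purpose of the study. Any pairwise PSM test added after seeing a significant result would have no stated multiplicity control.

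**Working it through.** **Inputs.** From Sample Size Determination: difference δ = 0.25, SD σ = 0.5, normal outcome, α = 0.05 with Dunnett's correction, power 0.75, 54 per model arm, prospective control 108, control PSM rate about 20%. Assumption: the one control group in the chi-squared test is the prospective one; 54 controls are also tried.

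**1. Reproducing 54 per arm.** For two comparisons with a shared control, the correlation is ρ = n_model / (n_model + n_control). The critical value c comes from the bivariate normal.

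- *Equal groups, one-sided, power for each comparison.* ρ = 0.5, c = 1.916. n = 2σ²(c + 0.6745)²/δ² = 2 × 0.25 × (1.916 + 0.6745)² / 0.0625 = 53.7, so 54. Power at 54/54/54 is 0.752.
- *Control 108, models 54 each, one-sided, power for both comparisons.* ρ = 54/162 = 1/3, c = 1.936. The standardised difference is 0.25 / (0.5 × √(1/54 + 1/108)) = 3.0. Power for each comparison is Φ(3.0 − 1.936) = 0.856, and for both jointly 0.754. The smallest size reaching 0.75 is exactly 54/54/108 = 216; adding 54 retrospective controls gives 270.

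Two-sided Dunnett at 0.05 does not return 54 (size per model arm for 0.75 power):

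| Control : model | Each comparison | Both | At least one |
|---|---|---|---|
| 1 : 1 | 67 | 84 | 48 |
| 2 : 1 | 51 | 65 | 34 |

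For example, with equal groups c = 2.212 and n = 8 × (2.212 + 0.6745)² = 66.7. So 54 points to one-sided testing, but by two routes that differ in allocation and power type.

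**2. Power of the planned test on the same inputs.** Noncentrality λ = Σ nᵢ(μᵢ − μ̄)²/σ², 2 degrees of freedom, critical value 5.99.

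| Control/model/model | Both models work | One model works |
|---|---|---|
| 54/54/54 | λ = 9.0, power 0.77 | λ = 9.0, power 0.77 |
| 108/54/54 | λ = 13.5, power 0.92 | λ = 10.125, power 0.82 |

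These are normal-scale figures, used only to compare tests on the stated inputs. An absolute fall of 0.25 cannot occur from a 20% control rate. That is a separate problem, and it affects either test.

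**3. What a significant result would show.** The Pearson test was simulated at 108/54/54 with control at 20%. The model-arm rates are illustrative assumptions.

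- *Printed 10%, virtual 30%:* significant in about 65% of trials. In about 33% of all trials it is significant while neither model beats control on one-sided Dunnett.
- *One model 20%, the other 40%:* significant in about 73%, with no benefit present.

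**4. Is power lost?** Same setting; the Dunnett columns give power for at least one contrast.

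| Scenario | Chi-squared | Two-sided Dunnett | One-sided Dunnett |
|---|---|---|---|
| Both models 20% to 10% | 0.417 | 0.421 | 0.549 |
| One model 20% to 10% | 0.297 | 0.285 | 0.377 |

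The gap appears only against one-sided testing.

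**The case against.** Four arguments on the other side have weight.

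- **Power.** A reader might infer that the three-group test wastes power. The documents do not support that. Against two-sided Dunnett the difference vanishes, and on the protocol's own inputs the chi-squared test exceeds 0.75. This objection stands.
- **Sidedness.** A reader might take it as fact that the study was sized one-sided. The article does not say so; it is inferred from which calculations return 54. This stands too.
- **Harm and direction.** Rejecting when the models are worse is a property of any two-sided test. With both models at 30% against 20%, two-sided Dunnett rejects in 36% of trials and the chi-squared in 32%. The reported PSM rates and intervals would show the direction. So the possibility of rejecting under harm is not in itself the fault. But descriptive rates are not planned contrasts against control and carry no multiplicity control.
- **Type I error and purpose.** A single test at 0.05 holds its level when all three rates are equal, so it would be wrong to say that the planned test inflates error. Printed against virtual is also an explicit aim in the Discussion, which a three-group null covers and Dunnett alone does not. Both points stand, and are reasons to keep the three-group test in a supporting role.

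The feasibility label and the possible existence of a fuller analysis plan do not remove the point. The article itself states a significance level, a power, a multiplicity method and a test, and these do not belong together.

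**Conclusion.** The mismatch holds and should be fixed, though it is not grave enough to block the study. The 0.75 does not describe the planned chi-squared test, whose power on the same normal inputs is about 0.77 with 54 controls and 0.82 to 0.92 with 108. A significant result would not establish that either model lowers PSM, or which one. The 33% figure shows the possible size of that gap, but it rests on assumed PSM rates and on one-sided Dunnett as the yardstick. The conclusion itself does not depend on sidedness: Dunnett contrasts and a three-group test address different hypotheses either way.

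**What to change.** In **Data Analysis**, name two primary PSM contrasts: printed against prospective control, and virtual against prospective control. Report each as a risk difference with a Dunnett-adjusted p-value and a simultaneous confidence interval. Keep the three-group chi-squared as supportive. Report printed against virtual as a difference with a confidence interval, since the Discussion makes that comparison an aim.

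In **Sample Size Determination**, state the sidedness and the type of power, and restate the power for that analysis. On the stated inputs at 108/54/54, one-sided Dunnett gives 0.86 for each comparison and 0.75 for both. Two-sided gives 0.78 for each and 0.64 for both. Reaching 0.75 for both with a two-sided test would need 65/65/130 = 260 prospective patients.

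The change costs one paragraph of wording and no extra patients or data if the present size is kept. The possible drawback is a less favourable stated power.
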